### Participant timeline {13}

As part of standard care, all patients will undergo a routine preoperative evaluation. Table 1 shows a full schedule of study-related activities and assessments in accordance with SPIRIT guidelines.

**Table 1 Tab1:** SOUL study participant schedule of activities

**Procedure**	**Prior to operation**	**Operative day (day 0)**	**Electronic survey assessments (days 1–10)**	**Electronic survey assessments (days 7–10)**	**Electronic survey assessments (days 22–42)**	**Electronic survey assessments (day 30)**
Informed consent	X					
Study education	X					
Demographics	X					
Medical History	X					
Randomization		X^a^				
Stent omission or placement		X				
EMA			X^1^			X
PRO survey	X^2^			X	X	
Patient survey on preferences/attitudes					X	

^1^Automated daily EMA invitations begin postoperative day 1 and continue through day 10 for all patients, with a final text sent on day 30 querying any patient-reported adverse events or unplanned healthcare utilization

^2^Preoperative PRO survey bundle should be completed within 30 days preoperatively

^a^For participants in the randomized cohort only

### Sample size {14}

The sample size was derived by the sample needed to power each co-primary endpoint for the RCT cohort. The larger sample size among the co-primary endpoints was used to estimate the final RCT cohort size. Each power calculation used a two-sided significance level of 2.5% to allow for two primary endpoints for a trial-level type I error of 5% as described below.

Postoperative days 7–10 PROMIS® Pain Interference change from pre-surgery is a co-primary endpoint; 101 participants per treatment arm will provide the RCT cohort with at least 90% power to detect a mean difference between stent placement vs. omission treatment groups of 5 points with an assumed standard deviation (SD) of 10 points, based on a two-sample *t* test (SAS 9.4), with a two-sided significance level of 2.5%. Previous work estimated that a clinically meaningful difference in PROMIS® Pain Interference is 2–6 points [25, 26]. A pilot study at our institution found an initial difference between stent omission and placement of 7.2 points with a SD of 13 for change and a SD of 10 at each time point. We expect our pilot may overestimate the treatment effect. Thus, we have targeted a difference of 5 points to represent a clinically significant target. A 10% loss to follow-up (failure to respond to the 7–10-day questionnaire) is assumed. Thus, 112 patients are needed per arm (total 224 patients). After consent, we estimate that 15% of patients who plan to be randomized will be unable to do so owing to intra-surgical factors that deem the procedure as complicated requiring 264 patients consented to the randomization cohort to attain 224 randomized patients.

Unplanned healthcare utilization within 30 days of ureteroscopy is the second co-primary endpoint.

With a modest probability of improvement in the reduction of healthcare utilization in ureteroscopy with stent omission, the impact in morbidity reduction and cost reduction would be great. There are no current estimates in the literature that help inform a minimum important difference for the win ratio estimate of healthcare utilization, our co-primary endpoint. So, we reasoned that a marginal probabilistic index, which is the effect size measure corresponding to the nonparametric Mann–Whitney *U* statistic that is used to test the hierarchical composite “win ratio” endpoint [27], of at least 67%, would be impactful as the study could conclude that a randomly chosen participant with stent omission has a two-thirds or greater probability of lower healthcare utilization than a randomly chosen participant treated with a stent. In the RCT with a two-sided 2.5% alpha and requiring 90% power to detect a treatment effect of 67%, 72 patients would be required per treatment arm. The sample size is based on the Finkelstein and Schoenfeld methods [28] for analysis of hierarchical composite endpoints, later called the win ratio by Pocock et al. based on the nonparametric Mann–Whitney *U* statistic [29]; the formula is provided in Yosef et al. [30].

The observational cohort sample size was derived from an assumption that 1/3 of patients approached and consented would be willing to be randomized. Thus, the observational cohort will consist of the estimated 2/3 (528) of patients who are approached and decline the RCT. With those assumptions, we find the following power for each primary endpoint.

Approximately 85% (449) of the observational cohort consented patients are expected to undergo an eligible ureteroscopy. From our prior data, approximately 70% (314) of these patients will receive a stent during ureteroscopy, and 135 (30%) will have stent omission. Assuming a 10% loss-to-follow-up (days 7–10 pain interference questionnaire not completed), this will result in 283 stent placement patients and 121 stent omission patients evaluable for the primary analysis of the observational cohort. Assuming a two-sided 2.5% type I error for each primary endpoint, 283 patients in the stent placement arm and 121 patients in the stent omission arm will provide 99.1% power to detect a clinically meaningful difference of 5 points between treatment arms for the change from pre-surgery in PROMIS® pain interference measure at days 7–10, assuming a standard deviation of 10 using a two-sample *t*-test. Sensitivity to the stented proportion and proportion agreeing to randomization (Table 2) demonstrates at least 84% power to detect a clinically significant difference in pain interference.

**Table 2 Tab2:** Observational cohort power with sensitivity to our assumptions

Proportion agrees to randomization (total approached)	Proportion stented	Sample size total (stented:stent omission)	Power
33% (792)	70%	404 (121:283)	99.1%
	50%	404 (202:202)	99.7%
	25%	404 (101:303)	99.1%
50% (528)	70%	202 (141:61)	84.2%
	50%	202 (101:101)	90.0%
	25%	202 (51:151)	86.7%

The power estimates presented assume that each observation is independent. However, due to surgeon preference in the observational cohort, there may be a potential for clustering which could impact the power of the study. We expect that surgeons within a site may behave more similarly and the variability between sites will be the correlation that will be important. The intraclass correlation (ICC) across multiple studies and therapeutic areas has been shown to likely be small, with a range between 0.01 and 0.05 [31]. Using our planned sample sizes, we can estimate the sample size needed under a range of ICCs using a method described by Klar and Donner [32] with an estimate of the sample size inflation factor (IF) based upon the ICC and the average sample size per cluster. Table 3 provides the power from using the effective sample size and the assumed proportions for each arm (stent vs stent omission using standard power calculations for the two-arm mean difference using a *t*-test with a two-sided type I error of 0.025 with the assumptions used for Pain Interference described above.

**Table 3 Tab3:** Power for pain interference co-primary endpoint in observational cohort with clustering effect (ICC), assuming 14 participating sites

Proportion agrees to randomization	Total approached	Final observational cohort sample size	Proportion stented	ICC group			
				**0**	**0.01**	**0.02**	**0.05**
33%	792	404	70%	99.1%	96.5%	92.3%	76.3%
			50%	99.7%	98.6%	96.1%	83.7%
			25%	99.1%	94.4%	89.0%	71.0%
50%	528	202	70%	84.2%	78.6%	73.4%	59.6%
			50%	90.0%	85.8%	81.2%	68.0%
			25%	86.7%	73.5%	68.0%	54.2%

For the co-primary endpoint of healthcare utilization in the observation cohort, if we assume that the stented proportion is 50%, with 202 participants per treatment group and a two-sided 2.5% type I error (alpha), we have 90% power to detect a treatment effect, marginal probabilistic index, of 60.1%. If the stented proportion is as low as 25% or as great as 75%, then we can infer that with 90% power, we will be able to detect a treatment effect between 60.1% and 64.3% as the sample size will be at least 101 per stent group.

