### Outcomes {12}

Outcomes will be assessed and analyzed similarly in both the randomized and observational cohorts within the study. SOUL has two co-primary outcomes:Patient-Reported Outcomes Measurement Information System (PROMIS) Pain Interference (Short Form 6b) T-score, change at postoperative days 7–10 compared to preoperative scoreUnplanned stone treatment-related healthcare utilization within 30 days of ureteroscopy; a hierarchical composite comprised of:◦Intensive care unit (ICU) care during hospitalization◦Unplanned hospitalization◦Unplanned additional procedure related to ureteroscopy: operating room or interventional radiology procedure◦Emergency department visit◦Unplanned clinic visit and/or diagnostic testing (urine testing and/or imaging)◦Number of ambulatory patient–provider interactions: phone calls/EMR messages

Secondary outcomes include the following:ICU care within postoperative day 30Unplanned hospital admission within postoperative day 30Unplanned additional procedure within postoperative day 30Emergency department visit within postoperative day 30Unplanned ambulatory urology office visit and/or diagnostic testing (urine testing and/or imaging) within postoperative day 30Number of ambulatory patient-provider interactions: phone calls/EMR messages within postoperative day 30PROMIS Pain Interference (Short Form 6b) T-scores change at postoperative 4–6 weeks compared to preoperative scorePROMIS Pain Intensity (Short Form 3a) T-scores change at postoperative days 7–10 and 4–6 weeks compared to preoperative scoreSymptoms of Lower Urinary Tract Dysfunction Research Network (LURN) Symptom Index (SI-10) change at postoperative days 7–10 and 4–6 weeks compared to preoperative scoresInternational Consultation on Incontinence Questionnaire Satisfaction (ICIQ-S) scores at postoperative days 7–10 and 4–6 weeksNumber of days taken off work by patients and caregivers during the first 7 days after ureteroscopy

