#### Randomized cohort analysis

A linear (ANCOVA) model will be used on the intention to treat (ITT) population to compare the two treatments, with PROMIS Pain Interference *t*-score at postoperative days 7–10 as the dependent variable and treatment group, stratification factor (stone location [kidney or ureter]) and pre-surgery (baseline) Pain Interference *t*-score as the independent variables [33]. The adjusted parameter estimate for treatment group (stent omission vs. placement) will be reported with the associated 97.5% CI and *p*-value (based on a type 3 *F*-test) that allows testing the hypothesis that Pain Interference differs between the two treatment groups. Multiple imputation will be used to address missing data and will be described fully in the statistical analysis plan. Sensitivity analysis will be conducted with the same analysis in the pain-modified intent-to-treat (PmITT, see Sect. 20c) population to assess the robustness of the effect found in the primary analysis. Additional sensitivity analysis will be conducted if there is baseline imbalance.

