#### Randomized cohort analysis

The analysis of the hierarchical composite endpoint of healthcare utilization using the Win Ratio [29] in the RCT will use the ITT population and will use the unmatched approach [35, 36]. The composite healthcare utilization metric within 30 days will be an assigned score for each patient based upon the highest ureteroscopy-related utilization level that they participate in with levels defined in decreasing order: (6) Hospitalization and ICU care; (5) unplanned hospitalization; (4) unplanned additional operating room or interventional radiology procedure; (3) emergency department (ED) visit; (2) ambulatory encounter: clinic visit; and (1) number of ambulatory patient/provider interactions. Then the rank of each patient in the stent omission arm will be compared to each patient in the stent arm using the unplanned healthcare utilization ranking rules described above such that each pair will have a winner. Summary statistics for the hierarchical composite win ratio endpoint will be presented, including the number of total pairs, and number and proportion of pairs that favor stent omission for each component of the unplanned healthcare utilization outcome. The number of winners and losers for stent omission and corresponding win ratio will be reported with the 97.5% (bootstrapped-based) confidence interval and *p*-value based on the Chi-square statistic. In addition, the probability of a participant with stent omission doing better than a participant with a stent will be presented. It is not expected to have missing data for this endpoint but if there is then multiple imputation will be used. Sensitivity analysis will be conducted with the same analysis in the healthcare utilization modified intent-to-treat (HCUmITT, see Sect. 20c) population to assess the robustness of the effect found in the primary analysis.

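### An equal 2.5% split between the two co-primaries is valid, but Holm's step-down test would gain some power at the same 5% error and the same sample size

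*Protocol article*

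**What the plan says.** Under Outcomes {12}, "SOUL has two co-primary outcomes": the change in PROMIS Pain Interference at days 7–10, and a hierarchical composite of unplanned healthcare utilization within 30 days. Sample size {14} sets the multiplicity rule: "Each power calculation used a two-sided significance level of 2.5% to allow for two primary endpoints for a trial-level type I error of 5"%. For pain interference, "101 participants per treatment arm will provide the RCT cohort with at least 90% power" for a difference "of 5 points with an assumed standard deviation (SD) of 10 points", "with a two-sided significance level of 2.5"%. Utilization is sized at the same level: 72 per arm for 90% power at a marginal probabilistic index of 67%. The observational cohort power figures also use 2.5% per endpoint.

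The analysis sections carry this level through. For pain in the randomized cohort, "The adjusted parameter estimate for treatment group (stent omission vs. placement) will be reported with the associated 97.5% CI". For utilization, the "corresponding win ratio will be reported with the 97.5% (bootstrapped-based) confidence interval". The observational win ratio also gets a 97.5% interval. The article mentions no step-down, recycling of alpha or gatekeeping, and does not require both endpoints to succeed.

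**The concern.** Either endpoint can carry a claim, so the 5% has to be protected. The article describes no way to reuse the error once one endpoint has succeeded. On that reading, a co-primary with a p-value between 0.025 and 0.05 is not significant even when the other is clearly positive. Holm would allow the second claim with the same 5% guarantee and no extra patients. Both endpoints are primary objectives, and the Introduction hypothesizes improvement in both, so power for the second claim has some value to this trial.

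**Working it through.** **Inputs.** From Sample size {14}: two-sided 2.5% per endpoint; pain difference 5, SD 10, 101 evaluable per arm; index 67%, 72 per arm; 112 randomized per arm. "A 10% loss to follow-up (failure to respond to the 7–10-day questionnaire) is assumed", which gives 101/0.9 = 112.2, stated as 112. The article expects no missing utilization data, so utilization is taken at 112 per arm. The correlation between the two test statistics is not given; 0 to 0.4 is assumed.

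**Step 1: reproduce the plan.**
- Pain, two-sample t test (noncentral t), 101 per arm: power 90.1% at 2.5%. The stated figure reproduces. At a full 5% the same test has 94.2%, which is the ceiling for any procedure that gives pain at most 5%.
- Utilization, Mann–Whitney (Noether) formula with 1:1 allocation: N = (2.2414 + 1.2816)² / [12 × 0.25 × (0.67 − 0.5)²] = 12.411 / 0.0867 = 143.2, or 72 per arm. This also reproduces.
- Utilization at 112 per arm: the mean of the test statistic is √(3 × 224) × 0.17 = 4.407. Power is Φ(4.407 − 2.241) = 98.5% at 2.5% and Φ(4.407 − 1.960) = 99.3% at 5%.

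**Step 2: Holm against the equal split.** Holm rejects an endpoint if its p ≤ 0.025, or if its p ≤ 0.05 and the other endpoint has p ≤ 0.025. With independent statistics:
- Pain: 90.1% + (94.2% − 90.1%) × 0.985 ≈ 94.1%.
- Utilization: 98.5% + (99.3% − 98.5%) × 0.901 ≈ 99.2%.
- Both, equal split: 0.901 × 0.985 ≈ 88.8%.
- Both, Holm: 0.942 × 0.993 − (0.942 − 0.901) × (0.993 − 0.985) ≈ 93.5%.

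A simulation with bivariate normal statistics (4 million draws, pain calibrated to 90.1%) gives:

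| Scenario | Power for | Equal split | Holm |
|---|---|---|---|
| Design effects | Pain | 90.1% | 94.0–94.1% |
| | Utilization | 98.5% | 99.0–99.2% |
| | Both | 88.8–89.2% | 93.5–93.6% |
| | At least one | 99.4–99.9% | 99.4–99.9% |
| Index 60% (assumed) | Utilization | 64% | 72–73% |
| | Both | 57–60% | 69–71% |
| Utilization null | Pain | 90.1% | 90.2–90.3% |

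Ranges cover correlation 0 to 0.4.

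**Step 3: error.** When both nulls are true, Holm makes at least one false rejection exactly when Bonferroni does: 4.9% at correlation 0 and 4.8% at 0.4, for both procedures. When only pain is null and utilization has its design effect, Holm's error on pain is 4.9–5.0%. The 5% guarantee holds under any dependence; the simulation only illustrates it.

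**The case against.** The strongest reply is that nothing here is wrong. An equal split is a disclosed, valid choice, it meets the plan's own 90% target for each endpoint, and its 97.5% intervals always agree with its tests. Under Holm, an endpoint that passes only at the second step can have a 97.5% interval that includes the null. All of this stands.

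It is also fair that the sample size text is a sizing statement and that a 97.5% interval is not a rejection threshold. The SAP, which is not shown, could already specify a step-down test. So the equal split is the natural reading of the article, not a rule it spells out.

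Four stronger readings are tempting and should be resisted:
- A reader might infer from the pilot SD of 13 for change that pain is badly underpowered at 2.5% and that Holm rescues it. The planned analysis is an ANCOVA on the day 7–10 score adjusted for baseline, not a test of raw change. The pilot SDs (10 at each time, 13 for change) imply a correlation of 1 − 169/200 = 0.155 and a residual SD of 10 × √(1 − 0.155²) ≈ 9.9. Power at 2.5% is then about 91%.
- A reader might infer that Holm permits a smaller trial. It does not: pain gets the 5% level only after utilization has passed at 2.5%.
- A reader might take the power for both as power for the trial's success criterion. The article lists two separate objectives and does not require both.
- A reader might treat the gain as assured. The background cites a Cochrane review with a trend for stenting to reduce unplanned visits, and if utilization shows no benefit the gain for pain almost vanishes.

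**Conclusion.** This is a cheap improvement and not an error. The scheme described amounts to Bonferroni, which Holm dominates on rejections at the same 5% familywise error; that result needs no assumption about correlation. The sizes do rest on assumptions. At the article's design effects the gain is about 4 percentage points for pain, under 1 point for utilization, and about 4.5 points for both. It would be about 9 points for utilization, and 10 to 12 for both, if the index were 60%, but that value is an assumption for the randomized cohort, which is designed on 67%.

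**What to change.** State in the SAP, and in the protocol if it is amended, before data lock:

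*Within each cohort, the smaller of the two co-primary p-values is tested at two-sided 2.5%. Only if it is significant is the other tested at two-sided 5%.*

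Keep the planned 97.5% intervals as simultaneous intervals. Report Holm-adjusted p-values, to be compared with 5%: twice the smaller p-value, capped at 1, and for the other endpoint the larger of that value and its own p-value. Add a footnote that an endpoint passing only at the second step may have a 97.5% interval that includes the null. Leave the sample size unchanged.

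The cost is a sentence and a footnote, with no added patients or data. Timing matters: recruitment began in June 2023 and the trial is unblinded, so a late change could look data-driven. A protocol amendment would need IRB approval and funder review under item {25}. If the SAP already specifies a step-down test, it is enough to say so in the protocol.

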### Interim analyses {21b}

An interim analysis after 396 patients are accrued is planned for confirmation of assumptions and re-estimation of sample size and power. Measures to be assessed include the proportion of patients who agree to join the randomization trial arm, the overall standard deviation of the primary endpoint, pain interference at days 7–10 change from pre-surgery, the proportion stented in the observational arm, and the intraclass correlation (ICC) in the observational arm. The sample size and power of each trial cohort will be reassessed based upon the interim analysis estimates compared to the assumed estimates. The results will be shared with the trial team and discussed with the funder.

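### Power for the pain co-primary gives SD 10 to a change score whose pilot SD was 13; the RCT size still suits the planned ANCOVA, but the interim is set to check the wrong SD

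*Protocol article*

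**What the plan says.** **Endpoint and power basis.** The protocol article, Sample size {14}, names the day 7–10 change from pre-surgery in PROMIS Pain Interference as the endpoint. It claims that "101 participants per treatment arm will provide the RCT cohort with at least 90% power" for a difference "of 5 points with an assumed standard deviation (SD) of 10 points", by two-sample t test. On alpha it says "Each power calculation used a two-sided significance level of 2.5% to allow for two primary endpoints".

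**Pilot.** The same paragraph reports the pilot result as "7.2 points with a SD of 13 for change and a SD of 10 at each time point". It explains why the target difference was lowered from 7.2 to 5. It does not explain why 10 was used for the SD and not 13.

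**Observational cohort.** The power statement for 283 and 121 patients again pairs change from pre-surgery with SD 10 and a t test. Table 3 carries the same assumptions forward.

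**Analysis.** The randomized cohort analysis of pain interference says: "A linear (ANCOVA) model will be used on the intention to treat (ITT) population to compare the two treatments". The dependent variable is the day 7–10 score, with baseline score and stone location as covariates.

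**Interim.** Interim analyses {21b} says: "An interim analysis after 396 patients are accrued is planned for confirmation of assumptions and re-estimation of sample size and power". One quantity to be estimated is "the overall standard deviation of the primary endpoint, pain interference at days 7–10 change from pre-surgery". Interim estimates are then compared with the assumed ones, and the results go to the trial team and the funder.

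**The concern.** Three parts of the plan use different quantities. The power statement describes a t test on change but uses the SD of a single score. The analysis is an ANCOVA, whose precision depends on the residual SD given baseline. The interim estimates the SD of change.

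If the pre/post correlation is low, as the pilot suggests, the SD of change is well above the single-score SD, while the residual SD stays close to it. An interim that compares the SD of change with 10 would then appear to show that the variance assumption had failed, although the planned analysis would be as precise as intended. The risk is an unneeded extension of the RCT, or a statement to the funder that it is underpowered.

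**Working it through.** **Inputs (Sample size {14} unless noted).** Difference 5; two-sided alpha 0.025; power 90%; 101 evaluable per arm; assumed SD 10; pilot SD 13 for change and 10 at each time point; 10% loss to follow-up; 15% found ineligible during surgery; 1:1 allocation (Explanation for the choice of comparators {6b}). Power is from the noncentral t distribution.

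**1. The plan's own figure.** With SD 10, the required n is 100.56, so 101 per arm, with power 90.1%. Then 101/0.9 = 112.2 (stated 112), and 224/0.85 = 263.5 (stated 264). The observational 283:121 gives 99.05% (stated 99.1%). The figures reproduce as stated.

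**2. The same t test with the pilot SD of change.**
- Power at 101 per arm with SD 13: 68.2%.
- n for 90%: 169.06, so 170 per arm. 170/0.9 = 188.9, so 189 per arm or 378 randomized. 378/0.85 = 444.7, about 445 consented.
- Against the plan: 378/224 = 1.69, which agrees with the variance ratio (13/10)² = 1.69.

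**3. The planned ANCOVA.** With the same SD at both times, Var(change) = 2 × SD² × (1 − r).
- 169 = 200 × (1 − r), so r = 0.155.
- Residual SD = 10 × √(1 − 0.155²) = 9.88.
- Power at 101 per arm: 90.9%. n for 90%: 98.2, so 99 per arm.

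**4. Sensitivity to rounding of the pilot SDs.** With the change SD between 12.5 and 13.5 and the single-time SD between 9.5 and 10.5, the ANCOVA needs 90 to 108 per arm. The t test on change needs 157 to 183.

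**5. Observational cohort under the stated t test with SD 13, before clustering.**

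| Stented : omitted | SD 10 | SD 13 |
|---|---|---|
| 283:121 (base case) | 99.1% | 90.1% |
| 141:61 (50% agree to randomization) | 84.2% | 60.0% |

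These rows show only what the stated test would give. The observational analysis also adjusts for baseline, so the SD 13 column is not its expected power.

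**6. What the interim would see.** If the pilot holds, the estimated SD of change is near 13 and the only assumed SD is 10. Putting 13 into the stated t test gives the 69% increase of step 2. The ANCOVA requirement of step 3 is unchanged.

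**7. A residual SD fitted without treatment.** In a 1:1 trial, leaving out treatment adds (difference/2)² to the variance. Under a true 5-point difference: √(9.88² + 2.5²) = √103.85 = 10.19, which would suggest 105 per arm instead of 99. This inflation is small beside that of step 6, but should be allowed for.

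**The case against.** **The stated calculation is arithmetically correct.** This stands. With the SD as written, 101 per arm gives 90.1%. The 68% appears only when the pilot's SD of change replaces 10. The fault is in what the SD is said to describe.

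**A reader might infer that the RCT is underpowered.** The documents do not support that. The primary analysis adjusts for baseline, and on the pilot's own figures an SD near 10 is about right for it.

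**A reader might infer that the interim will enlarge the trial by 69%.** The documents do not support that either. The interim section gives no formula, threshold or automatic increase; results are discussed with the team and the funder. The 69% needs an interim SD near 13 and reuse of the t test, and it concerns only the RCT. Re-estimation details may properly sit in the SAP. What the protocol does fix is the quantity to be estimated and that it is compared with the assumed value, and that quantity does not match the primary model.

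**A correlation of 0.155 is falsely precise.** This stands in part. It comes from two rounded SDs, and the size of the pilot is not given. Step 4 shows that the conclusion survives rounding, but 0.155 should not be written in as an established value.

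**The interim trigger might also seem wrong.** Half of 792 is 396, which assumes one third agree to randomization, whereas 78 of the first 162 enrolled (48%) are in the randomized cohort. This is not an error. The look also serves the agreement rate, the proportion stented and the observational ICC. An earlier look tied to the number randomized would leave fewer observational patients for the ICC. Tables 2 and 3 already cover 50% agreement.

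**Conclusion.** The point holds as a mismatch between the power statement, the primary model and the interim quantity. The power statement attaches a single-time-point SD to a change score. Taken literally with the pilot SD of 13, its t test has about 68% power at 101 per arm and needs 170.

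The planned RCT size is adequate for the planned ANCOVA, with about 91% power. This assumes that the pilot SDs are representative, that the SD is equal at both times, and that the correlation is the same in both arms. Within rounding, 90 to 108 per arm are needed, so 101 falls slightly short only towards the upper end.

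The consequence that matters is a possible false signal at the interim of about 69% more RCT patients. It is conditional, not prescribed. The observational base case keeps about 90% power even at SD 13, before clustering.

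**What to change.** 1. **Sample size {14}, RCT.** State the power as ANCOVA of the day 7–10 score on baseline, with residual SD about 10, giving 90% at 101 per arm. Say that 10 is not the SD of change, which was 13 in the pilot.
2. **Sample size {14}, observational cohort.** Make the same correction to the SD wording in the observational power statement and in the text leading to Table 3.
3. **Interim analyses {21b}.** Replace the SD of change with the residual SD of the day 7–10 score given baseline and stone location, and compare that with 10. If it is estimated without treatment in the model, allow for the inflation (about 10.2 under a true 5-point difference) before reading a shortfall into it.

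The interim trigger can stay at 396. The cost is wording in two sections and one model fit at the interim. No extra patients are needed, and if the residual SD is pooled without treatment, no comparison of arms is revealed.

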## Trial status

Recruitment commenced on 1 June, 2023. The current protocol is Version 1.0 of 1 June, 2023. As of May 30, 2024, we have enrolled 162 total patients (78 in the randomized cohort and 84 in the observational cohort). Enrollment is estimated to complete on June 2025.

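### The 25%-stented entries of Table 2, repeated at ICC 0 in Table 3, do not reproduce at the stated 2.5% alpha, so the claimed minimum of 84% power is wrong

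*Protocol article*

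**What the plan says.** All the relevant statements are in the protocol article under Sample size {14}.

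- **Alpha.** The section opens with a general rule: "Each power calculation used a two-sided significance level of 2.5% to allow for two primary endpoints". It repeats the level for the observational cohort ("Assuming a two-sided 2.5% type I error for each primary endpoint, 283 patients in the stent placement arm") and again for Table 3 ("with a two-sided type I error of 0.025 with the assumptions used for Pain Interference described above").
- **Effect, SD and test.** The base case is given as "99.1% power to detect a clinically meaningful difference of 5 points between treatment arms", with an SD of 10 and a two-sample t-test.
- **Table 2.** Six scenarios are listed. With 404 evaluable patients: 99.1% (70% stented, 121 and 283 per group), 99.7% (202:202) and 99.1% (25% stented, 101:303). With 202 evaluable patients: 84.2% (141:61), 90.0% (101:101) and 86.7% (25% stented, 51:151).
- **Summary of Table 2.** The text concludes that the sensitivity analysis "demonstrates at least 84% power to detect a clinically significant difference in pain interference".
- **Table 3.** It repeats the six values in its ICC 0 column and adds ICCs of 0.01, 0.02 and 0.05, assuming 14 sites.

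**The concern.** Table 2 cannot be right as printed, and this shows before any software is used. With total sample size, difference, SD and alpha held fixed, a two-sample t-test loses power as the split becomes more unequal. A 51:151 split is more unequal than 141:61 at the same total of 202, yet it is given more power (86.7% against 84.2%). In the same way, 101:303 is more unequal than 121:283 at a total of 404, yet both are given 99.1%.

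Table 3 shows the same fault from another side. In the block of 202, the 25%-stented row falls from 86.7% at ICC 0 to 73.5% at ICC 0.01, a drop of 13.2 points. The 70% and 50% rows beside it fall by only 5.6 points (84.2 to 78.6) and 4.2 points (90.0 to 85.8).

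At stake is the one sentence that sums up Table 2. Its purpose is to give the worst case for a co-primary endpoint across the planned scenarios. In addition, the planned interim analysis ({21b}) compares the observed agreement proportion, stented proportion, SD and ICC with the assumed ones. The agreement proportion, stented proportion and ICC are the axes of these tables, so the tables are a natural reference for that reassessment.

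**Working it through.** **Inputs, all from Sample size {14}.** Difference 5; SD 10; two-sided alpha 0.025; group sizes as printed in Table 2; 14 sites for Table 3.

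**Formula.** Noncentrality = 5 / (10 × √(1/n1 + 1/n2)), with n1 + n2 − 2 degrees of freedom. Power is the probability that a noncentral t variable falls beyond the two-sided critical value. The order of the two groups does not matter.

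**Step 1: Table 2 at the stated alpha and at 5%.** The critical value at 2.5% is 2.250 for 402 degrees of freedom and 2.258 for 200. At 5% it is 1.966 and 1.972.

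| Split | Noncentrality | Printed | Two-sided 2.5% | Two-sided 5% |
|---|---|---|---|---|
| 283:121 | 4.60 | 99.1% | 99.05% | 99.6% |
| 202:202 | 5.02 | 99.7% | 99.7% | 99.9% |
| **101:303** | 4.35 | **99.1%** | **98.2%** | **99.14%** |
| 141:61 | 3.26 | 84.2% | 84.15% | 90.1% |
| 101:101 | 3.55 | 90.0% | 90.1% | 94.2% |
| **51:151** | 3.09 | **86.7%** | **79.6%** | **86.70%** |

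Four entries reproduce at 2.5%, to within 0.1 point. The two 25%-stented entries do not; they match the 5% column to the printed decimal.

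Worked through for 51:151: √(1/51 + 1/151) = 0.1620, so the noncentrality is 0.5 / 0.1620 = 3.087. With 200 degrees of freedom and critical value 2.258, power is 79.6%. With critical value 1.972 it is 86.7%.

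**Step 2: could a different split explain the printed values?** At 2.5%, a total of 202 needs a split of about 69:133 or 70:132 to give 86.7%. A total of 404 needs about 123:281 to give 99.1%. These are about 34% and 30% in the smaller group, so no common proportion near 25% explains both.

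**Step 3: Table 3 with ICC above 0.** The article describes an inflation factor built from the ICC and the average cluster size. Taking it as IF = 1 + (N/14 − 1) × ICC, with effective N = N/IF and alpha 0.025, the 25%-stented rows come out as follows.

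| N | ICC | IF | Effective N | Printed | Two-sided 2.5% | Two-sided 5% |
|---|---|---|---|---|---|---|
| 404 | 0.01 | 1.279 | 316.0 | 94.4% | 94.4% | 97.0% |
| 404 | 0.02 | 1.557 | 259.4 | 89.0% | 89.0% | 93.5% |
| 404 | 0.05 | 2.393 | 168.8 | 71.0% | 70.9% | 79.9% |
| 202 | 0.01 | 1.134 | 178.1 | 73.5% | 73.5% | 82.0% |
| 202 | 0.02 | 1.269 | 159.2 | 68.0% | 68.0% | 77.5% |
| 202 | 0.05 | 1.671 | 120.9 | 54.2% | 54.5% | 65.6% |

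All 18 cells with ICC above 0, including the 70% and 50% rows, agree with the 2.5% calculation to within 0.4 points. In Table 3 the fault is therefore confined to the two ICC 0 cells carried over from Table 2.

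**Step 4: consistency after correction.** With 79.6% at ICC 0, the 25%-stented row for N = 202 falls by 79.6 − 73.5 = 6.1 points to ICC 0.01, in line with its neighbours.

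**Step 5: the summary sentence.** The smallest corrected entry of Table 2 is 79.6%, which is below 84%.

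**The case against.** The strongest reply is that nothing in the design depends on these cells. The sample size was set by the randomized cohort: 101 evaluable per arm gives 90.1% power at 2.5%, as claimed. The observational base case of 283:121 also reproduces. The article expects about 70% stented from prior data, so 25% is an extreme scenario. The 101:303 error is 0.9 points at a power above 98%. The 51:151 result misses 80% by 0.4 points, and a normal approximation gives 80.1%. All of this stands. It limits the consequence but does not make the printed values or the 84% statement correct.

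Several stronger readings are tempting, and the document does not support them.

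- **That the whole 25%-stented rows of Table 3 are wrong.** Only their ICC 0 cells are.
- **That a 5% alpha was demonstrably used.** This is inferred from the match; a one-sided 2.5% test gives the same numbers. What can be shown is that the entries do not reproduce at the stated alpha.
- **That the 84% was taken from the wrong 86.7%.** It corresponds to the 141:61 cell, 84.2%, which is correct. The claim fails because the corrected 51:151 cell lies below it.
- **That the trial is already in the faulty cell.** Trial status reports "we have enrolled 162 total patients (78 in the randomized cohort and 84 in the observational cohort", so 78/162 = 48% joined the randomized cohort, close to the 50% block. But the faulty cell also needs 25% stented, which nothing in the article suggests. The row in that block that matches the expected 70% is correct.
- **That the loss of power from clustering is concealed.** Table 3 prints it openly, down to 54.2%.

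**Conclusion.** The point holds as a narrow arithmetic correction. At the stated two-sided 2.5% alpha, the 25%-stented entries should read 98.2% instead of 99.1% (0.9 points too high) and 79.6% instead of 86.7% (7.1 points too high). Each wrong value is printed twice, in Table 2 and in the ICC 0 column of Table 3. The statement of at least 84% power is false for the range of scenarios it summarizes, whose true minimum is about 79.6%.

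This rests on the article's own difference, SD, alpha, test and group sizes. That the cells are wrong does not depend on why; the 5% alpha is the likely cause, not an established one. A reader might infer that the trial, or the observational cohort as planned, is underpowered. That does not follow: the correction concerns sensitivity scenarios only, and the randomized sample size and the 283:121 base case are unaffected.

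**What to change.** 1. In the 25%-stented rows of Table 2 and the matching ICC 0 cells of Table 3, replace 99.1% by 98.2% (101:303) and 86.7% by 79.6% (51:151).
2. Reword the summary sentence after the base case to claim at least 79% power assuming independent observations, and refer to Table 3 for the effect of clustering.
3. Leave the cells with ICC above 0, the base case and the randomized cohort's calculation as they are.

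The cost is two values, each in two places, and one sentence. Sample size, conduct and analysis do not change. The stated worst case becomes less favourable by about 4 to 5 points (84.2 − 79.6 = 4.6).
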